**Fig. 1 Fig1:**
[figure not shown]
CONSORT diagram

Any adult registered on the Scottish Bowel Screening database with ability to consent (aged 50–74 years) will be included in the participant selection, but invitations will not be sent to those who have recently participated in screening, or will shortly be invited for screening (within six months of either event). This is to avoid any potential confusion between the study materials and the actual screening result.

For ethical reasons, the Study Participant Information Sheet will state that those currently being treated for cancer or other serious illness should ignore the invitation and accept our apologies for contacting them at what may be an inappropriate time. Inclusion on the screening database coincides with the first invitation at age 50, thus it is not possible to sample those not previously invited. Prospective participants would therefore include those who have previously been invited but not taken part in screening, those who have previously completed a gFOBt or FIT test, and also potentially a small number who have previously had a positive test and been offered colonoscopy.

Our aim is to develop novel, personalised risk information materials (for both risk of having CRC and risk of undergoing colonoscopy) which will be provided in a visual format (based on infographics [9]), aimed at being understandable across education levels, as guided by recommendations [10, 11]. It is planned to use absolute instead of relative risks, mortality instead of survival rates, and natural frequencies instead of conditional probabilities, as these are recommended as best practice [12]. However, this is open to change if the development process suggests otherwise.

The risk information materials for each of the study arms will be developed in months 1–12. We will recruit 2 Public and Patient Involvement (PPI) representatives to be core members of our project team and a further 4–6 PPI representatives to participate in co-development workshops along with the RF, the core project team and an infographics expert who has been engaged to design and produce the risk materials. The materials will then be pilot tested on sample participants before being refined and finalised.

The PPI participants will be from a healthy population group. They will be selected to be representative of the screening population with regard to socioeconomic status, age and gender. Those with a diagnosis of colorectal cancer will be excluded as it is important for the materials to be relevant to asymptomatic people who do not have a diagnosis of colorectal cancer. Medically qualified people will also be excluded. They will be sought via routes such as SHARE, the NHS Public Involvement Team and through other academic contacts with appropriate patient representative groups in place who might be interested in participating in this work.

The co-development workshops will be held throughout months 3–12 to develop, review and refine the project materials. We estimate that this would involve up to six three-hour meetings, which will be held at a venue convenient to the PPI group. Travel and subsistence costs will be met in full. As key members of the workshops, the PPI participants will contribute to the development process from a lay perspective, as health professionals and patients may form different interpretations of risk information. They will also provide feedback on the modified informed choice measure. We do not think it necessary to audio record the discussions; however, the RF will minute key points and circulate to the group following each meeting.

The risk materials will be pilot tested with a small sample (*n* = 30) of participants from the screening database, who would be posted the study invitation letter with reply slip, patient information sheet, risk information materials and informed choice questionnaire in advance of the main recruitment (month 7). An option to consent to telephone contact is available on the reply slip. Telephone interviews (months 8–9) will be conducted with consenting participants to assess ease of understanding and acceptability, and understanding of levels or risk based on the different scenarios. The impact on informed choice via the developed measure will also be assessed. The results will be fed into the finalisation of the materials, at a workshop involving the PPI members (month 10).

Presentation or risk will be assessed both as a ‘1 in x risk’ and natural frequencies in the development process, one or both of these may be used in the final materials. Participants will also be presented with the information on the risks of having a colonoscopy which is currently provided to those who are offered the test following a positive gFOBT. Group 3 is effectively a control group, which reflects current practice, to allow comparison of likely uptake of colonoscopy with the personalised risk information groups. Three verbal categories (lowest, moderate, highest risk) for simplicity of presentation of information are proposed. However, it is possible this could be modified during the development process, if the PPI involvement suggests otherwise. The development of the risk materials is a key part of the project, thus it is not possible to be too specific on detailed content or categorisations at this stage. The finalised risk materials will be used in the RCT across Scotland.

Patients who complete and return the response form indicating that they are willing to take part will be randomised to one of the study arms and then posted the materials and informed choice questionnaire with a stamped addressed envelope for return of the questionnaire. Study documents which will be sent to the participant are: Scenario letter(s) according to study arm, study questionnaire, “Having a colonoscopy” leaflet and “The Bowel Screening Test” leaflet. Return of the questionnaire will be considered as an implied consent.

Randomisation with minimisation on variables related to risk (i.e. age, SIMD, gender) will be carried out via MINIM software by an individual independent to the process of running the study, who will thus be blinded to the recruitment process.

The study will be co-ordinated by a Study Management Group, consisting of the PI, Co-investigators, Research Fellow and two PPI members.

Consenting participants will be randomised to one of 3 conditions:Numerical (i.e. a personalised numerical-based risk assessment (e.g. 1 in x risk) related to hypothetical test result and age and gender)Categorical (as treatment group 1) but this would be categorised as ‘Lowest’, ‘Moderate’ and ‘Highest’ riskPositive cut-off (i.e. as current practice that is i.e. a positive test result, based on the current cut-off to give approximately 2% positivity).

Each condition would be presented with hypothetical scenarios relating to different levels of risk of CRC and asked to rate their intention of attending a colonoscopy if they received that result following an actual FIT. Three scenarios, relating to lowest, moderate and highest risk for colorectal cancer would be presented in groups 1 and 2; by definition group 3 has only one possible scenario i.e. a positive screening test result.

The lowest, moderate and highest risk categories and the disease frequencies used in the scenarios will be derived from data from a study which observed that risk of significant colorectal neoplasia rises with increasing faecal haemoglobin concentrations [13]. Although the actual faecal haemoglobin concentrations might represent different risks for individuals (e.g. different genders), the hypothetical scenarios would be presented as a specific level of risk (e.g. with this result you would have a 1 in x risk (or a moderate risk) of having CRC) and thus would be applicable to all participants. The aim of using both actual numerical risks and verbal categories is to assess their impact on the understanding and reactions of participants to these different forms of materials. The standard information describing the first-line screening process will be provided as an introduction to the different scenarios, as participants may have different previous experiences of first line screening.

A study questionnaire will be used to collect participant responses to information materials including intention, knowledge about the test (8 items: including risks of having cancer and undergoing a colonoscopy) and attitudes towards undergoing the test (4 items: including benefits, importance and pleasantness/ unpleasantness) and anxiety. Questionnaire data will be collected at a single time-point (months 19–21). Telephone interviews will be conducted in a small number of participants (10 from each study arm) to collect more detailed responses.

Data on screening history (i.e. previous participation/failure to participate/been offered a colonoscopy) will be collected at the time of sampling, as these strongly predict screening uptake [6]. We accept that recruitment via invitation letter may lead to a bias towards previous screening participants in our sample. However, in actual practice, the offer of informed choice following FIT would only be made to those who had completed the test with detected blood in their sample, so we believe this would be an acceptable, if not desirable, bias. However, as FIT has just been introduced in Scotland and the previous gFOBt is thought to be regarded as more difficult to complete [14], we would not want to exclude people who may complete a FIT in the future. Any differences with regard to previous screening history would be explored in our analysis (see below).

There is as yet no accepted measure of informed choice in cancer screening uptake [12]. Our *informed choice* measure will be adapted from Smith et al. [9]. They applied a multidimensional model of informed choice (developed and validated for antenatal screening for Down’s syndrome [15, 16], and combined the constructs of a) knowledge, b) attitudes and c) behaviour to assess the extent to which people made an informed choice about participating in screening using gFOBT. Items measuring knowledge about the test (8 items: including risks of having cancer and undergoing a colonoscopy) and attitudes towards undergoing the test (4 items: including benefits, importance and pleasantness/ unpleasantness) will be adapted to relate to colonoscopy rather than gFOBT. As this is therefore a new scale, the measure will be pilot tested with the PPI project participants, workshop participants and a small sample of participants from the bowel screening database (the same sample as in development of risk materials above) to assess acceptability and understanding. Full psychometric testing of the developed measure will be undertaken and reported.

We will use the informed subscore (items 1–3) from the Decisional Conflict Scale [17] to assess the extent to which participants feel informed about their decisions. These items are: “I know which options are available to me”, “I know the benefits of each option” and “I know the risks and side effects of each option”, scored on a 7-point scale from “strongly agree” to “strongly disagree”. As this is a hypothetical scenario study we are only able to use intention and not actual uptake as our outcome measure of behaviour. However, intention was very strongly related to actual uptake (with a mean intention score of 6.7 out of a maximum 7 for kit returners) in our previous large-scale study [6].

*Intention* to take up the offer of colonoscopy, as a proxy for behaviour, will be measured on a Likert-type scale from 1 (low intention) to 7 (strongly intend) in response to e.g. “If I received information that I had *x* level of risk of bowel cancer, I would choose to have a colonoscopy”. *Anxiety* will be measured by a previously-validated six-item version of the State Trait Anxiety Inventory [18]. An example item is the statement “I am worried”, with a choice of four responses on a scale from “not at all” to “very much”.

Ease of understanding and acceptability of the presentation of risk information will also be assessed in the questionnaire using Likert-type questions e.g. “I found the information presented easy to understand” scored on a 7-point scale from “strongly agree” to “strongly disagree”.

A small number of participants would be purposively sampled, from those agreed to be telephoned/consented for the interview, from each treatment arm (estimate *n* = 10 per arm, total *n* = 30) to provide representation with regard to age, gender, socioeconomic status and responses to the scenarios. The RF would conduct semi-structured interviews, by telephone, to explore the acceptability/readability and any potential negative impact of the risk information, participants’ understanding of risk factors and attitudes to the different scenarios presented, and reasons for their reported intentions. As only a small number of the 300 participants will be interviewed at follow-up, the questionnaire will include an open-ended final question encouraging additional comments. The follow-up telephone interviews will include questions relating to emotional responses to the material and understanding of what is meant by the verbal risk categories, as well as asking how participants perceive the risk of undergoing a colonoscopy versus that of having cancer in the given scenarios.

Telephone interviews are an effective means of gathering data in health research provided challenges are addressed [19]; and are more practical and cost-effective than face-to-face interviews as participants will be from the whole of Scotland. Interviews will be recorded (with permission) and fully transcribed.

All questionnaires and other records will be identified in a manner designed to maintain participant confidentiality. All records will be kept in a locked filing cabinet with limited access to study staff only. Archiving of study documents will be for five years after the end of study.

Data integrity of questionnaire data will be enforced by valid and range checks at the time of data entry. Clinical information will not be released without the written permission of the participant, except as necessary for monitoring and auditing by the Sponsor or its designee. All electronic information will be stored on secure network computers held on a University of Dundee network drive accessed by a password protected device. Data management will be conducted in compliance with Tayside Medical Science Centre (TASC) Standard Operating Procedures (SOP) on Data Management, TASC SOP53 Data Management Systems in Clinical Research.

The Data Management System (DMS) will be Excel, as approved by Sponsor. The DMS will be based on the protocol for the study and individual requirements of the investigators. Information will only be collected that is required to meet the aims of the trial and to ensure the eligibility and safety of the participant. The trial database will be compliant with TASC SOP53 Data Management Systems in Clinical Research. The anonymised data will be imported from Excel for analysis using SPSS (see below).

The database is managed in line with all applicable principles of medical confidentiality and UK law on data protection, namely, the Data Protection Act 1998, which brought UK law into line with the EU Data Protection Directive. The Data Controller will be the University of Dundee and the Data Custodian will be the PI. Database lock will be conducted in compliance with TASC SOP32 Locking Clinical Study Databases.

The PI, co-investigators and all institutions involved in the study will permit study related monitoring, audits, and Research Ethics Committee review. The PI agrees to allow the Sponsor or, representatives of the Sponsor, direct access to all study records and source documentation.

Knowledge, attitudes and intention to take up colonoscopy will be compared between the groups, using pre-determined categorisations [12], to assess whether providing personalised information on CRC risk leads to informed choice. In addition, between group differences in outcomes on the scales relating to knowledge, attitudes and behaviour will be analysed as continuous variables via Analysis of Variance (ANOVA) and individual items will also be examined, as recommended by Ghanouni et al. [20]. Covariates in the analyses are age, gender, deprivation category, and history of FOBT/FIT screening, as obtained from the screening database. Data on personal or family history of CRC are not available in the screening database and therefore cannot be examined.

Data on intention to take up colonoscopy from each scenario will be matched with the expected range of risk scores in the Scottish population (from the demonstration pilot of FIT as a First Line Test), to estimate total uptake, and hence the potential impact on colonoscopy services for numerical versus categorical presentation of personalised risk information, in comparison to the current positive/negative cut-off. This will provide preliminary evidence of the effects of implementing informed choice following introduction of FIT on current colonoscopy services.

Themes from the qualitative analysis will be compared between those who intended and did not intend to take up the offer of colonoscopy, which would help in understanding how the personalised risk information for both CRC and colonoscopy is understood and received and also the underlying reasons for the choices made. Any differences with respect to age/gender/socioeconomic status and also whether or not previously participated in screening and/or taken up the offer of colonoscopy will also be explored.

Thematic qualitative analysis will be used to analyse responses gathered from the telephone interviews as it permits rich description of participants’ perceptions, feelings and experiences [21]. Each interview will be analysed on a line-by-line basis for key themes/patterns. Recruitment will continue until saturation of themes is reached. The planned recruitment of *n* = 30 to the qualitative interviews is based on numbers required for saturation in previous research by the authors, but there is scope to increase this if saturation is not achieved.

An *n* = 300 (100 in each group) will have 83.7% power of detecting a 1 point increase in knowledge (intervention versus control), and a 2 point difference in attitudes (based on existing study means/SDs [9, 15]), using a one-way ANOVA. A pilot sample of 60–100 per group is recommended to provide an estimate of an event rate [22] (e.g. screening uptake); so a sample of 300 would provide an indicative effect size of colonoscopy uptake for a future full-scale study. We would send out 1440 invitations, from whom we conservatively expect to get around 360 replies (25%) (based on previous research [8]); we expect a further 20% attrition between consent and questionnaire return, giving a final *n* = 300. In the event that we do not hit our target of 360 replies to the first letter, a second wave of invitation letters would be sent out (the number of these would be based on actual response to and the deficit from the first invitation). We accept that the sample size may not be sufficient to assess all interactions between covariates. However this is a pilot study and a major aim is to assess effect sizes to determine accurate sample sizes for a larger study; we believe we have sufficient power to achieve this aim.

There is a risk of causing upset to patients with cancer or patients who may be disturbed by thinking about their cancer risk. It is not possible to exclude such patients from the initial contact. We have worded the Participant Information Sheet to express our apologies for contacting anyone in inappropriate circumstances. The patient invitation letter provides contact details of an individual who is completely independent of the research who can help in this case and advise to whom a complaint can be made to if required. It will also be stressed that risk scenarios are purely hypothetical. It should be noted that all individuals who will be contacted are enrolled in screening and the invite would not be dissimilar to the Scottish Bowel Screening invite.

If there is a problem with any participant it will be recorded in an Adverse Event log in compliance with TASC SOP11v9.

The PI will seek approval for any amendments to the Protocol or other study documents from the Sponsor, Research Ethics Committee (REC) and NHS R&D Office(s). Amendments to the protocol or other study docs will not be implemented without these approvals.

In the event that the PI needs to deviate from the protocol, the nature of and reasons for the deviation will be recorded in the Case Report Form, documented and submitted to the Sponsor. If this necessitates a subsequent protocol amendment, this will be submitted to the Sponsor for approval and then to the appropriate REC and lead NHS R&D Office for review and approval. In the event that a serious breach of Good Clinical Practice (GCP) or protocol is suspected, this will be reported to the Sponsor Governance Office immediately.

Annual reporting will be conducted in compliance with TASC SOP 15: Preparing and Submitting Progress and Safety Reports in CTIMPs and Non-CTIMPs, as a condition of sponsorship and as a condition of a favourable opinion from a REC. An HRA Annual Progress Report for NCTIMPs will be prepared and submitted by the CI to REC, and copied to the Sponsor, on the anniversary date of the REC favourable opinion.

Any safety reports additional to Serious Adverse Event reports, for example, reports of a Data Monitoring Committee, will be sent by the CI to REC, with a Safety Report Form, and to the Sponsor.

The end of study is defined as database lock once all data collection is complete. The Sponsor, CI and/or the SC have the right at any time to terminate the study for clinical or administrative reasons. The end of the study will be reported to the Sponsor and REC within 90 days, or 15 days if the study is terminated prematurely. The PI will ensure that any appropriate follow up is arranged for all participants. A summary report of the study will be provided to the Sponsor and REC within 1 year of the end of the study.

Ownership of the data arising from this study resides with the study team and their respective employers. On completion of the study, the study data will be analysed and tabulated, and a clinical study report will be prepared.

The clinical study report will be used for publication and presentation at scientific meetings. Investigators have the right to publish orally or in writing the results of the study.

Summaries of results will also be made available to Investigators for dissemination within their clinical areas (where appropriate and according to their discretion).

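### The six-month screening exclusion, as worded, leaves in people recently invited to screening whose kit is still unreturned, so study materials can reach someone with a real result pending

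*Protocol article*

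**What the plan says.** The eligibility paragraph of the protocol article's Methods, after Figure 1, says that study invitations will not go to "those who have recently participated in screening, or will shortly be invited for screening (within six months of either event"). The stated reason is: "This is to avoid any potential confusion between the study materials and the actual screening result".

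The next paragraph describes who remains: "Prospective participants would therefore include those who have previously been invited but not taken part in screening", along with people who have completed an earlier test and a few who have been offered colonoscopy. No minimum time since the last screening invitation is given. It also notes that "Inclusion on the screening database coincides with the first invitation at age 50".

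On timing, screening history "will be collected at the time of sampling, as these strongly predict screening uptake". In the main study the pack ("Scenario letter(s) according to study arm, study questionnaire" and two leaflets) is posted later, once the response form is back and the participant has been randomised. The pilot paragraph is different: the invitation letter, reply slip, information sheet, risk materials and questionnaire are listed as one posting.

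**The concern.** The rule exists to keep study materials away from people who may be expecting a real result. A person holding a live screening kit is such a person, yet neither trigger catches them: they have not participated recently, and their invitation lies in the past.

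The setting makes confusion possible. The study invitation is sent on behalf of the programme's director, the packs include programme leaflets, and the only scenario in group 3 is a positive result. The protocol itself describes its invitation as resembling the screening programme's own. Someone who took a hypothetical result for their own, or a real result for a study letter, could be distressed or misled. Their anxiety and intention answers would then reflect something other than the randomised presentation.

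**Working it through.** **Coverage of the rule, case by case**

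| Screening status at sampling | Participated in past 6 months? | Invitation due in next 6 months? | Excluded? |
|---|---|---|---|
| Returned a kit in the past 6 months | Yes | No | Yes |
| Due an invitation in the next 6 months | No | Yes | Yes |
| Invited in the past 6 months, kit unreturned | No | No | **No** |
| Invited more than 6 months ago, no kit returned, next invitation over 6 months away | No | No | No (as intended) |

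The third row is the gap. It includes people newly on the database at age 50, because entry coincides with their first invitation. Someone in that row who returns the kit after sampling stays in the study and can have a real result on the way.

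**Size**

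The plan gives no figure to reproduce, and it gives no screening interval, uptake or kit return time. The following is therefore an illustration on assumptions: a 24-month round, participation p = 60%, mean return time r = 1 month, and sampling in proportion to time spent eligible.

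- Participant: eligible from invitation to return (r months), excluded for 6 months after return, then eligible until 6 months before the next invitation. Eligible months = r + (18 − r − 6) = 12.
- Non-participant: eligible from month 0 to month 18 = 18 months.
- Average eligible months per person = 0.6 × 12 + 0.4 × 18 = 7.2 + 7.2 = 14.4.
- Share of the frame that has a kit outstanding and will return it = p × r / 14.4 = 0.6 × 1 / 14.4 = 4.2%.
- Main mailing: 1440 × 0.6 / 14.4 = 60 invitations. Among the 360 expected to be randomised, 15 if they reply at the same rate as others.
- Pilot: 144 × 0.6 / 14.4 = 6 invitations.

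Varying the assumptions:

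| Round | Participation | Mean return time | Share | Of 1440 |
|---|---|---|---|---|
| 24 months | 60% | 0.5 month | 0.3/14.4 = 2.1% | 30 |
| 24 months | 60% | 1 month | 0.6/14.4 = 4.2% | 60 |
| 24 months | 60% | 2 months | 1.2/14.4 = 8.3% | 120 |
| 36 months | 60% | 1 month | 0.6/26.4 = 2.3% | 33 |

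For the 36-month round, eligible months are 24 and 30, so the average is 0.6 × 24 + 0.4 × 30 = 26.4.

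These counts are of people who could have a result pending. Only those whose kit and study pack happen to coincide are exposed to confusion, so the number actually confused would be smaller.

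**The case against.** **The wording could be two-sided.** Six months of either event might mean a window on both sides of the participation date and the invitation date, and then recent invitees would be out. The list of remaining groups does not settle this, since it also names earlier test completers without a time limit although recent completers are clearly excluded. But the invitation trigger is written as something still to come, and the two-sided reading strains that. If it was intended, the text should say so.

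**There are safeguards.** Main-study participants opt in after reading an information sheet, the packs contain a study questionnaire, the protocol undertakes to stress that the scenarios are hypothetical, and an independent contact is named. Groups 1 and 2 receive three scenarios together, which makes it unlikely that one is taken as a personal result. All of this stands and keeps the point minor. It does not close the gap: the exclusion was adopted alongside these safeguards, group 3 sees a single positive scenario, and the pilot posting as described precedes any opt-in. The pilot's expected numbers (144 invited, 36 responding, 30 completing) follow the two-step pattern of the main study, so the pilot sequence is worth confirming.

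**Stronger readings that the documents do not support.** A reader might count everyone invited in the past six months who returns no kit in that round: 0.4 × 6 / 14.4 = 16.7%, or 240 of 1440. Those people never have a result pending, so they are not the group at risk. A reader might also infer from 18 against 12 eligible months that non-participants are over-represented 1.5-fold, contrary to the remark that the offer in practice "would only be made to those who had completed the test with detected blood in their sample". That does not follow. Sampling is purposive and weighted towards groups less likely to take part, non-participants are kept deliberately, the protocol expects a net bias towards previous participants, and screening history is a covariate.

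**Conclusion.** The gap holds on the plain wording: people invited to screening in the past six months with an unreturned kit are not excluded, although they can generate the very result the rule is meant to keep apart from the study. How many are affected cannot be derived from the documents. It is the late returners who matter, probably a small percentage of invitations: about 4% under the central assumptions, and about 2% to 8% across the alternatives shown. These shares ignore the purposive weighting and any difference in reply rates, both of which could move them.

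The consequence is a possible confusion for a few participants, with some contamination of their anxiety and intention answers. A reader might infer that the trial comparison is biased. The documents do not support that, since randomisation would spread such people across the arms. This is a minor eligibility correction, and the sample size and analysis figures are untouched.

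**What to change.** Reword the exclusion so that study invitations are withheld from anyone who, in the previous six months, was sent a screening invitation or returned a kit, or who is due a screening invitation in the next six months. State that it applies to the pilot, the main mailing and any second wave. With this filter, a second check of screening status before packs are posted is optional. It would matter mainly for the few who return a kit more than six months after being invited.

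The cost is one additional date filter on the screening database and a smaller eligible frame. Under the central assumptions, eligible months fall to 18 − 7 = 11 for participants and 18 − 6 = 12 for non-participants, an average of 0.6 × 11 + 0.4 × 12 = 11.4 against 14.4, or about a fifth less. The documents do not give the size of the database, but it is national and has to supply only 144 pilot and 1440 main invitations plus any second wave, so this should not limit recruitment.
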